### Sample Size

The sample size was calculated to detect a 20% absolute difference in the primary outcomes between the intervention and control arms. The calculation assumed a baseline prevalence of EBF of 48% [3] and AACF of 50% [39] in the control group. Using a 2-sided significance level of 5%, statistical power of 80%, a 1:1 allocation ratio, and an anticipated 20% loss to follow-up in each study arm, a total sample of 300 pregnant women (150 per arm) was determined to be sufficient to detect the expected intervention effect. Loss to follow-up included participant withdrawal and/or discontinuation of app use in the intervention arm. Sample size estimation was performed using *OpenEpi* software (version 3.0).

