#### Primary Outcomes

The primary end points of the study are (1) EBF at 6 months of infant age and (2) introduction of AACF [49,50] at 6 months of infant age.

In addition, EBF will also be assessed at the 6th, 10th, and 14th weeks, while CF practices will also be assessed at 9 months of infant age. The repeated assessments at additional time points will be used for longitudinal analyses to evaluate trends and sustainability of feeding practices over time. Operational definitions of the primary outcome measures are provided in Table 3.

**Table 3. T3:** Operational definitions of primary and secondary outcome measures.

Outcome	Operational definitions
Primary outcomes [49,50]	
Exclusive breastfeeding	Proportion of infants who are fed exclusively with breast milk up to 6 months of age
Introduction of age-appropriate complementary feeding	Proportion of infants who are introduced to solid, semisolid, or soft foods at 6 mos of age
Secondary outcomes	
Infant and young child feeding practices [49,50]	
Early initiation of breastfeeding	Proportion of children put to the breast within 1 hour of birth
Minimum dietary diversity	Proportion of children 6‐12 months of age who receive food from 4 or more food groups
Minimum meal frequency	Average number of daily meals for children 6‐12 months of age, who receive solid, semisolid, or soft foods
Minimum acceptable diet	Composite variable based on meal frequency and dietary diversity
Mean duration of breastfeeding	Average duration an infant is breastfeeding for 12 months
Continued breastfeeding at 1 y	Proportion of children 12 months of age who are still on breast milk
Child health	
ARI^a^	Short, rapid breathing that is chest-related and/or difficult breathing that is chest-related. Percentage of children up to 1 year of age with symptoms of ARI at any time in the last 2 weeks preceding the follow-up
Acute diarrhea	Passage of 3 or more loose or liquid stools per day (or more frequent passage than is normal for the individual). Percentage of children up to 1 year of age with symptoms of diarrhea at any time in the last 2 weeks preceding follow-up
Visit to the emergency room	Infant brought to the emergency room for management of any acute illness in past 2 weeks.
Hospitalization	Infant admitted to the hospital for diagnosis or management of any acute illness in past 2 weeks.

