The extent and patterns of missing data will be examined. If more than 10% of outcome data are missing, multiple imputation using chained equations will be performed under a missing-at-random assumption. Imputed results will be compared with complete-case analyses in sensitivity analyses. Prespecified subgroup analyses will assess effect modification by maternal education, employment status, and parity through inclusion of interaction terms. All analyses will be conducted using Stata software (StataCorp), with statistical significance set at .05.

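### Two primary outcomes are each tested at a flat .05, and the plan does not say whether one or both must be significant for the app to be called effective

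*Protocol article*

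**What the plan says.** Under Primary Outcomes the protocol article lists two end points: "The primary end points of the study are (1) EBF at 6 months of infant age and (2) introduction of AACF", the second also at 6 months. Footnote e of Table 2 confirms that both 6-month assessments are primary.

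The Sample Size section treats them as a pair: "The sample size was calculated to detect a 20% absolute difference in the primary outcomes between the intervention and control arms". The control rates are given separately: "The calculation assumed a baseline prevalence of EBF of 48% [3] and AACF of 50% [39] in the control group". The error rates are given once: "Using a 2-sided significance level of 5%, statistical power of 80%, a 1:1 allocation ratio", together with "an anticipated 20% loss to follow-up in each study arm". The total is 300 women, 150 per arm.

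The Data Analysis Plan gives each primary outcome a regression model, a 95% confidence interval and a two-sided P value, and sets one level for everything: "All analyses will be conducted using Stata software (StataCorp), with statistical significance set at .05". The article contains no alpha split, no ordering of the two outcomes, no multiplicity procedure and no statement that both must succeed. The Abstract's Conclusions and the Discussion nevertheless look ahead to a single verdict on whether the intervention is effective.

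**The concern.** With two primary tests and one verdict, the decision rule fixes the operating characteristics of the trial.

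- If one significant result out of two is enough, testing each at .05 raises the chance of a false claim above the nominal 5%.
- If both must be significant, the type I error is protected, but the power that matters is the chance of winning on both. That is a different quantity from the 80% in the Sample Size section.

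The text allows either reading, so neither the error rate nor the power of the trial's main conclusion is defined. If the choice is made after the results are known, it can follow the data. The article intends the findings to inform national nutrition policy, so the criterion for calling the app effective should be fixed beforehand.

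**Working it through.** **Inputs from the Sample Size section.** Two-sided alpha .05; power 80%; control rates 48% (EBF) and 50% (AACF); difference 20 points, so 48 vs 68% and 50 vs 70%; 20% loss; 150 per arm, leaving 150 × 0.8 = 120 evaluable. The correlation between the outcomes is not given, so it is an assumption, shown as a range.

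**Step 1: the plan's own size.** Let p̄ be the mean of the two rates p₁ and p₂, and d = |p₂ − p₁|.

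n per arm = [1.960·√(2p̄(1−p̄)) + 0.842·√(p₁(1−p₁)+p₂(1−p₂))]² / d²

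- EBF: 95 per arm; 95/0.8 → 119; total 238 (264 with continuity correction).
- AACF: 93 per arm; 93/0.8 → 117; total 234 (258 with continuity correction).

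The stated 300 is not reproduced, but it exceeds every one of these, so the statement that 300 is sufficient is true on the stated inputs.

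**Step 2: error rate if either outcome can carry the claim.** Under independence it is 1 − 0.95² = 0.0975. For correlated test statistics (bivariate normal, both null hypotheses true):

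| absolute correlation | at least one false positive |
|---|---|
| 0 | 9.75% |
| 0.3 | 9.5% |
| 0.5 | 9.1% |
| 0.8 | 7.8% |
| 0.9 | 7.0% |

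Counting only errors in the app's favour, under independence: 1 − 0.975² = 0.0494, against 0.025 for one test.

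**Step 3: power per outcome at 120 evaluable per arm.**

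Power = Φ{[d − z·√(2p̄(1−p̄)/n)] / √((p₁(1−p₁)+p₂(1−p₂))/n)}

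- EBF at .05: (0.20 − 1.960 × 0.06372)/0.06240 = 1.204, power 88.6%.
- EBF at .025: (0.20 − 2.241 × 0.06372)/0.06240 = 0.916, power 82.0%.
- AACF at .05: (0.20 − 1.960 × 0.06325)/0.06191 = 1.228, power 89.0%.
- AACF at .025: (0.20 − 2.241 × 0.06325)/0.06191 = 0.941, power 82.7%.
- With continuity correction (d reduced by 1/n) at .025: 78.3% and 79.0%.

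**Step 4: Holm's procedure when both effects are real.** Simulation with 1,000,000 draws at 120 per arm and correlations 0 to 0.6 gives 86 to 88% per outcome, 92 to 97% for at least one and 79 to 81% for both. Against 88.6% and 89.0% unadjusted, the cost is about one to three points per outcome.

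**Step 5: joint power if both must succeed at .05.** Under independence, 0.886 × 0.890 = 0.789. It is 77.6% at a correlation of −0.6 and 82.1% at +0.6.

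**Step 6: sensitivity to what the 20% loss means.** The Sample Size section counts discontinuation of app use as loss, while the analysis is by intention to treat, so these women stay in. Assume that the whole 20% is app discontinuation and that these women revert to the control rate. The intervention rates become 0.8 × 68 + 0.2 × 48 = 64% and 0.8 × 70 + 0.2 × 50 = 66%, with all 150 per arm analysed:

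- EBF (48 vs 64%): (0.16 − 1.960 × 0.05732)/0.05657 = 0.843, power 80.0% at .05; with 2.241 in place of 1.960, 0.557, power 71.1% at .025.
- AACF (50 vs 66%): (0.16 − 1.960 × 0.05699)/0.05624 = 0.859, power 80.5% at .05; with 2.241, 0.574, power 71.7% at .025.

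All figures are for unadjusted comparisons of two proportions.

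**The case against.** The strongest reply is that this is an omission that a statistical analysis plan would fill: the article is condensed, and Holm's procedure itself works at an overall .05. That has some force, since a multiplicity rule may exist elsewhere. But the article does not leave the level open. It sets .05 for all analyses, and a plan that tests the smaller P value against .025 would depart from that text. A plan that requires both would leave the stated 80% without its apparent meaning. Either way the article's text needs a sentence.

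A reader might infer that the trial's false-positive rate is nearly 10%. The documents do not support that as a flat statement. It holds only under an either-outcome rule that the article never states, and the Discussion's description of the expected contribution mentions EBF and AACF together, which fits a both-outcomes rule equally well. It is also close to the upper bound: both outcomes describe the same infant's feeding at the same visit, and correlation lowers the figure.

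A reader might also infer that 300 women leave spare sample that already pays for Holm. That is not established. It holds with the uncorrected formula and 120 evaluable per arm, falls slightly short with continuity correction, and fails if the loss is mostly app discontinuation. Nor is a total of 300 an error because it exceeds 234 to 264: exceeding a minimum does not contradict the stated power.

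Finally, each outcome will be reported with its own interval and P value, so readers could apply Holm themselves. That limits the harm, but it does not define what the trial will claim.

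**Conclusion.** The point holds, at the level of something that should be fixed. The article fixes two separate primary outcomes and a flat .05 without a success rule.

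Under an either-outcome rule, the chance of at least one false positive is 9.75% under independence and about 7.0 to 9.5% for absolute correlations of 0.9 down to 0.3. In the app's favour alone, under independence, it is about twice what a single two-sided 5% test allows. Under a both-outcomes rule the error is at most 5% and no adjustment is called for, but the power to be stated is the joint one: about 79%, range 78 to 82%, at 120 evaluable per arm with the full 20-point effect on both outcomes.

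These figures rest on an assumed range of correlations and on unadjusted two-proportion tests. The power figures also depend on how the 20% loss divides between missing data and app discontinuation, which the article does not say. No estimate, design feature or data collection is affected.

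**What to change.** Before primary outcome data are analysed, add one of the following to the Data Analysis Plan.

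1. **Either outcome can be claimed.** Each primary outcome is claimed only if it passes Holm's procedure at an overall two-sided 5%: the smaller P value is tested against .025 and, if that succeeds, the other against .05. State in the Sample Size section that power at Holm's first step is conditional: about 82 to 83% per outcome with 120 evaluable per arm and the full 20-point effect, 78 to 79% with continuity correction, and as low as about 71 to 72% if the 20% loss is app discontinuation that dilutes the effect under intention to treat.
2. **Both must succeed.** State that rule, keep .05 for each, and give the joint power of about 79% under independence (78 to 82% for correlations of −0.6 to 0.6) at 120 evaluable per arm, with the same caution about dilution.

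Limit the blanket .05 statement so that it does not override the chosen rule.

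The cost is a few sentences and no extra participants. Holm costs about one to three points of power per outcome when both effects are real. When only one is real, the cost approaches the gap between the two levels (88.6 − 82.0 = 6.6 points for EBF, 89.0 − 82.7 = 6.3 for AACF). The both-outcomes rule costs no alpha, but the trial then fails if either outcome misses.

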#### Patient and Public Involvement Statement

Patients and the public are not involved in the design, recruitment, or implementation of this study. Study participants will be informed about the results through awareness seminars conducted at the study site.

### Ethical Considerations

The study approval has been granted by the institutional Ethical Review Committee (Ref 2022-3424-20757, received on February 6, 2025) and the National Bioethics Committee for Research (Ref 4‐87/NBCR-1114/23/204, received on August 15, 2025). In the event of any protocol deviations or amendments, the Ethical Review Committee will be notified and approval will be sought. Written informed consent will be obtained from all eligible participants prior to enrollment by the RA at recruitment. Participants will be provided with detailed information regarding the study objectives, procedures, potential risks and benefits, data usage, and confidentiality protections. They will also be given adequate opportunity to discuss the study, ask questions, and clarify any concerns before providing consent. Participants will be informed that participation is voluntary and that they may withdraw at any time without any effect on their routine care. Consent will be documented electronically and via signed consent forms before installation of the mHealth app.

## Results

The study has been approved by the Ethical Review Committee of the Aga Khan University and the National Bioethics Committee. Participant recruitment started on February 2, 2026. As of May 14, 2026, we have recruited 230 participants. Follow-ups and outcome assessments are expected to be completed by June 2027, and analysis is expected to be completed by September 2027. We expect the results to be published by December 2027.

## Discussion

### Expected Contributions and Future Implications

This study is expected to provide evidence regarding the effectiveness of a culturally tailored mHealth intervention in improving EBF and AACF during the first year of infant age, while repeated longitudinal assessments may provide insights into the sustainability of feeding behaviors over time. Previous mHealth interventions conducted in Nigeria, Nepal, Indonesia, and Pakistan have primarily demonstrated improvements in maternal IYCF knowledge, breastfeeding awareness, and user satisfaction [23-27]; however, evidence regarding sustained behavioral outcomes remains inconsistent [28-30]. Systematic reviews from LMICs further highlight substantial heterogeneity and limited longitudinal evidence regarding sustained IYCF outcomes [31-34]. This study addresses these gaps by evaluating a theory-informed, culturally tailored mHealth intervention through an RCT for sustained feeding practices during the infant’s first year of life in Pakistan, where rigorous evidence on digital nutrition interventions remains limited. If found effective, the intervention may offer a scalable and potentially cost-effective strategy for strengthening maternal and child nutrition services in Pakistan and similar LMIC settings. Study findings will be disseminated through peer-reviewed publications, scientific conferences, and engagement with health care providers, policymakers, and public health organizations to support evidence-informed digital health programming and nutrition policy development.

### Limitation

We acknowledge limitations in our study. First, participation is limited to literate women who own smartphones, which may restrict generalizability. However, this criterion is necessary to ensure valid exposure to the digital intervention and to evaluate its feasibility under real-world conditions. Second, despite restricted onboarding and backend access controls, some degree of information sharing between intervention and control participants may occur in community settings. Such contamination will be monitored through usage analytics and addressed analytically using intention-to-treat and sensitivity analyses. Third, behavioral outcomes may be subject to recall or social desirability bias. To mitigate this, standardized questionnaires, repeated assessments, and objective app usage metrics will be used where feasible. Fourth, sustained engagement with the app over the 1-year intervention period may decline due to digital fatigue or competing demands. Automated reminders and regular RA contact are incorporated to support adherence and maintain engagement. Fifth, blinding of participants and research staff is not feasible due to the nature of the intervention, which may introduce observer or reporting bias. However, this risk will be minimized through standardized outcome assessment procedures, structured questionnaires, RA training, and blinded data analysis using coded group allocation. Finally, the study assesses intervention effectiveness over a 1-year period and does not evaluate long-term sustainability or scalability. Findings will inform future studies designed to assess broader implementation and longer-term impact.

### Strengths

This study’s strengths include its rigorous 2-arm parallel-group randomized controlled design, the first randomized trial in Pakistan, to evaluate the efficacy of an mHealth app targeting EBF and age-appropriate IYCFPs, thus addressing a critical national evidence gap. The intervention is theory-driven, culturally tailored, and aligned with WHO and UNICEF guidance, enhancing relevance and acceptability. Longitudinal follow-up from late pregnancy through the infant’s first year allows assessment of both early initiation and sustained feeding behaviors. Objective monitoring of intervention exposure through backend analytics strengthens internal validity beyond self-reported measures, while provision of standard-of-care F2F counseling in both arms enables estimation of the incremental benefit of the mHealth intervention. Finally, the use of widely available smartphone technology enhances scalability and policy relevance within Pakistan’s expanding digital health ecosystem.
